### Secondary objectives

To determine if the intervention:i.increases clinicians’ adherence to the Australian Cancer Pain Management in Adults Guidelines’ screening and assessment recommendations;ii.increases the quality of clinicians’ pain assessment documentation;iii.increases clinicians’ cancer pain assessment capabilities (knowledge and confidence); andiv.is cost-effective compared with standard cancer and palliative clinician CPD activities at reducing cancer patients’ reported pain scores from a healthcare systems perspective.

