#### Control group

Consenting participants randomised to the wait-listed control group will complete all of the data collection measures but will not have access to the intervention until the intervention arm participants at each site have completed the trial and all data collection has been completed. It is anticipated that the control group participants will have access to the intervention within 16 weeks of the trial commencing at each site.

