### Methods: data collection, management and analysis

#### Data collection methods

Data will be collected at three time points during the trial—Time 1 (T1), Time 2 (T2) and Time 3 (T3) (Table 1)—as described below.

**Table 1 Tab1:** Study activities at each time point

	Study time			
	Baseline (T1)	Intervention	T2	T3
	*Immediately before intervention commencing*		*Immediately following the completion of the intervention*	*12 weeks after completion of the intervention*
Study activities				
Chart audit data collection	X		X	X
Online Participant Survey (Self-PAC Survey)	X		X	
Economic data collection	X		X	X
Wait-listed control group access online module				X

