##### Participant survey

The Self-PAC survey has undergone preliminary validation [40] and will be administered at two study time points (T1 and T2) in an online format. This instrument has three distinct sub-scales with Cronbach’s alpha reporting high internal consistency reliability: seven-item pain assessment knowledge (0.944); three-item pain assessment tool knowledge (0.846); and seven-item pain assessment confidence (0.919) scales [36]. To promote participant retention, project officers will send a unique survey link to all participants and send reminder emails to participants who do not complete the survey within the required time frame, at both survey time points.

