#### Statistical methods

##### Statistical analysis plan

An intention-to-treat analysis will be applied to all primary and secondary outcomes. Missing data will be imputed using Multiple Imputation by Chained Equations. Should an imbalance in clinicians’ characteristics be found between groups at baseline, these characteristics will be included in the final analyses as covariates. A significance level of 5% will be adopted for refuting all test hypotheses. The intervention and wait-listed control arms will be compared on the primary and secondary outcome measures.

The primary endpoint (reduction in mean pain NRS scores) will be analysed using the Linear Mixed Method with a repeated measures approach and possible adjustments to patients’ and staff characteristics to compare the mean change in patient pain NRS scores from admission to discharge or audit date between the intervention and control groups across different time points.

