The secondary endpoints will be analysed as follows:i.The frequency of comprehensive pain assessment between the intervention and control will be determined by differences between groups. As the outcome variable is a count variable without a fixed bound, Poisson regression with possible adjustments for covariates will be applied to the data.ii.A quality score will be calculated for each audited record across time and entered into the patient’s medical records. This score will reflect the quality of the pain documentation in the medical notes and will be calculated using seven items of documentation (pain severity score, location, radiation, aggravating and alleviating factors, quality and timing). One mark will be assigned to an item identified in the medical records and a summative quality score will then be calculated to represent the total amount of information recorded. A higher quality score represents a larger amount of pain assessment information recorded and a greater adherence to recommended pain assessment practices. The quality of pain assessment documentation will be determined by comparing the quality scores across time and between groups using a General Linear Model with repeated measures.iii.The mean scores of the three domains of the Self-PAC survey (pain assessment knowledge, pain assessment tool knowledge and pain assessment confidence) will be compared across time and between the intervention and control groups using the General Linear Model with repeated measures approach and with possible adjustments for covariates effects.iv.The primary objective of the cost-effectiveness analysis is to evaluate the incremental resource use, cost and consequences of adding the mHealth enabled pain assessment performance feedback intervention to standard clinician CPD activities to improve cancer pain control. A Markov decision model will be developed to estimate the cost-effectiveness of the mHealth intervention from a healthcare perspective. Healthcare resource utilisation and cost data will be estimated from a systematic literature review of the direct and indirect costs of pain in cancer patients including hospitalisations, emergency department visits, outpatient clinic appointments, medications, GP visits and investigations. Responder rates will be estimated from the project. The modelled economic evaluation will provide estimates of the incremental cost-effectiveness ratio (incremental cost per additional responder, response = a 2-point mean reduction in NRS pain score or 30% reduction in pain intensity) and the incremental net monetary benefit (INMB; monetary value of additional effects of care minus the additional costs of care) [42] at potential threshold values for responder rates and cost-effectiveness acceptability curves. Model sensitivity to variations in individual inputs and overall decision uncertainty will be assessed through probabilistic sensitivity analyses.

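### Self-PAC (objective iii): the repeated-measures model does not name the deciding term, and comparing T2 scores adjusted for T1 would be more powerful at no cost

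*Protocol article*

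**What the plan says.** Secondary objective iii (Secondary objectives) asks whether the intervention "increases clinicians’ cancer pain assessment capabilities (knowledge and confidence"). The Participant survey section says the Self-PAC "will be administered at two study time points (T1 and T2) in an online format", and Table 1 places T1 "Immediately before intervention commencing". Under Control group, wait-listed clinicians "will complete all of the data collection measures but will not have access to the intervention until" the intervention arm at their site has finished and data collection is complete. Both arms therefore supply a pre-intervention and a post-intervention score, and the controls' T2 score is unexposed.

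The Statistical analysis plan section says in general that "The intervention and wait-listed control arms will be compared on the primary and secondary outcome measures". For Self-PAC it says the three domain means "will be compared across time and between the intervention and control groups using the General Linear Model with repeated measures approach", with possible covariate adjustment. For the primary endpoint the same section is more specific: it compares the mean change in pain scores "between the intervention and control groups across different time points". The Self-PAC sentence has no counterpart to that contrast.

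**The concern.** Objective iii concerns the effect of the intervention. With randomised arms and a T1 score taken beforehand, the quantity that answers it is the arm difference at T2. A repeated-measures model with a time factor and an arm factor has three terms: time, group and group-by-time. The Self-PAC sentence names two directions of comparison and does not say which term decides. The terms differ in what they estimate and in power:

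- The **group main effect** compares each arm's average over T1 and T2. No intervention effect is possible at T1, so the average carries half of the T2 effect.
- **Group-by-time**, with two occasions, is the difference between arms in T2 minus T1. It targets the right quantity but subtracts the whole T1 score, which adds noise unless T1 and T2 are very highly correlated.
- The **time main effect** pools both arms and says nothing about the intervention.

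What is at stake is the power and precision of the answer on a secondary outcome, and the possibility of choosing the term after seeing the results.

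**Working it through.** **Plan figure.** There is none to reproduce for Self-PAC. The 35 per arm under Sample size (45 after inflation) was derived for the pain NRS and is used here only as a plausible number analysed; 45 less 25% attrition is 33.75, or about 34.

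**Inputs from the article.** Two occasions, T1 before the intervention (Participant survey, Table 1); 1:1 randomisation (Allocation); 5% significance ("A significance level of 5% will be adopted for refuting all test hypotheses"), taken as two-sided because sidedness is not stated.

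**Assumed inputs.** SD 1 at both occasions; T1–T2 correlation rho of 0.3, 0.5 or 0.7; true T2 effect d of 0.5 or 0.75 SD.

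**Formulas**, with n per arm:

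- Group main effect: estimates d/2, SE = sqrt((1 + rho)/n). Put on the scale of d, the variance factor per clinician is 2(1 + rho).
- Group-by-time: estimates d, SE = sqrt(4(1 − rho)/n). Variance factor 2(1 − rho).
- T2 adjusted for T1: estimates d, SE = sqrt(2(1 − rho²)/n). Variance factor 1 − rho².

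**Variance relative to the adjusted analysis**

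- Group-by-time: 2(1 − rho)/(1 − rho²) = 2/(1 + rho), which is 1.54, 1.33 and 1.18 at rho 0.3, 0.5 and 0.7.
- Group main effect: 2(1 + rho)/(1 − rho²) = 2/(1 − rho), which is 2.86, 4.00 and 6.67.

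**One case by hand** (n = 35, rho = 0.5, d = 0.5; normal approximation, power ≈ Φ(z − 1.96)):

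- Group: z = 0.25/sqrt(1.5/35) = 0.25/0.207 = 1.21, power about 23%.
- Group-by-time: z = 0.5/sqrt(2/35) = 0.5/0.239 = 2.09, power about 55%.
- T2 adjusted for T1: z = 0.5/sqrt(1.5/35) = 0.5/0.207 = 2.42, power about 68%.

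**Simulation** (10,000 runs per cell, t-based tests, no common trend). Ranges run over rho 0.3 to 0.7:

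| n per arm, effect | Group main effect | Group-by-time | T2 adjusted for T1 |
|---|---|---|---|
| 35, 0.5 SD | 20–25% | 42–75% | 58–82% |
| 35, 0.75 SD | 39–48% | 74–98% | 90–99% |
| 45, 0.5 SD | 25–31% | 52–86% | 69–91% |

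At n = 35, rho = 0.5 and d = 0.5 the simulated values are 22%, 54% and 66%, in line with the hand calculation. With no intervention effect, all three tests reject in about 5% of runs, so all three are valid.

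**Time main effect.** With no intervention effect but a rise of 0.3 SD in both arms, it is significant in 55–89% of runs at n = 35. This shows only that it cannot stand in for a test of the intervention.

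**The case against.** The strongest reply is that the sentence is ordinary shorthand. A repeated-measures model with time and arm normally includes their interaction; the article never mentions main effects and never excludes group-by-time; and the deciding term may be named in an SAP that is not shown. That is largely right. The missing term alone would not be a finding, and group-by-time would be a valid test. What stands is that, even on this reading, the stated model treats T1 as an outcome, so its interaction is a change-score test that uses T1 less efficiently than adjustment does. The planned covariate adjustment does not clearly recover the loss: T1 Self-PAC is already an outcome in the model, and adjustment is triggered by baseline imbalance in clinicians' characteristics.

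A reader might go further and infer three things that the document does not support:

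- **That neither main effect tests the intervention.** The group main effect does, because arms are randomised and any T1 difference is chance. It keeps its 5% error and is only diluted.
- **That objective iii could be met with no effect.** This needs the pooled time effect to count as success. The article does not say so, and its general rule that the arms are compared points the other way.
- **That the economic result would be wrong.** Self-PAC is listed among the efficacy data, but the incremental cost-effectiveness ratio is per pain responder, defined on the NRS.

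It is also fair that a large effect would show under any of the terms: at 1.0 SD and 34 per arm, even the group main effect has 60–71% power.

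**Conclusion.** This is a free improvement to a secondary analysis, not an error that invalidates it. Compared with T2 adjusted for T1, at 35 per arm and a 0.5-SD effect, group-by-time loses about 16 points of power at rho 0.3 (42% against 58%) and about 6 at rho 0.7 (75–77% from simulation and formula, against 82–83%). The group main effect loses about 33 points at rho 0.3 (25% against 58%) and about 62 at rho 0.7 (20% against 82%).

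The halving of the group effect follows from the design alone. The variance ratios 2/(1 + rho) and 2/(1 − rho) need only equal SDs at T1 and T2. The power figures rest on the assumed effect, correlation and number analysed, none of which the article gives for Self-PAC. Which term the investigators intend cannot be settled from the article.

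**What to change.** Replace the Self-PAC sentence under secondary endpoint iii with wording such as: *For each Self-PAC domain, the T2 score will be compared between the randomised arms in a linear model with the T1 score of the same domain as covariate, together with any other planned covariates and using the planned multiple imputation. The adjusted arm difference at T2 with its 95% CI is the test for objective iii. Changes over time within arms are descriptive.*

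The cost is one sentence. T1 and T2 scores are already collected in both arms, so no new data, visits or sample size are needed. The wording should be fixed before outcome data are compared by arm. Like the current text, it leaves open how the three domain results combine into one answer on objective iii; that can be settled at the same time.

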
##### Interim analysis

An interim analysis will be undertaken immediately after 25 participants have completed the intervention with data collected at T2. At this time, the corresponding 25 clinicians in the control arm will also be assessed for T2 data collection as described in the protocol. The reasons for nominating a sample of 25 in both intervention and control arms are: (1) based on the concept that an interim analysis is recommendable at the halfway point of the trial (i.e. half of the RCT sample have completed the trial); (2) given that the total participants in each arm has been estimated to be 45, half of the sample will only be about 22 clinicians. This sample size would not be sufficient to support an accurate and precise comparison between groups. To ensure sufficient power for the interim analysis, a sample of 25 in each arm is considered reasonable. In order to stop the trial, we would need to demonstrate significant results of comparison between groups with an effect size of a reduction in mean patient-reported pain rating by at least 1.5 units in the intervention arm at an alpha level of 5% and preferably at 1%.

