### Sample size

Informed by our pilot work [30, 31] and based on a standard RCT design [41], it is estimated that a sample size of 35 participants in each arm is required. This assumes a 5% significance level and 90% power of the study with an effect size of a reduction of mean patient-reported pain rating of 1.5 (+ 2.0). Allowing for an attrition rate of 25%, and 5% for possible inclusion of covariates in the analyses, will increase the RCT sample size to 90 clinicians (45 in each arm). To achieve the trial objectives, it is estimated that 90 cancer and/or palliative care clinicians, with half (*n* = 45) in each arm is required.

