## Trial status

Protocol Version 1.2_2018.05.29.

Recruitment to commence: 1 September 2018.

Approximate recruitment completion: 31 July 2019.

Refer to Additional file 4 for items from the World Health Organization Trial Registration Data Set.

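### The interim look is justified as halfway by setting 25 completers against 45 enrolled per arm; like for like it falls at up to about 71–74% of evaluable clinicians at T2, and none need have finished the trial

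*Protocol article*

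**What the plan says.** The Interim analysis section sets the look when 25 intervention clinicians have completed the module and have T2 data. The corresponding 25 controls are assessed at the same time. The first reason given is that "an interim analysis is recommendable at the halfway point of the trial (i.e. half of the RCT sample have completed the trial". The second is that "given that the total participants in each arm has been estimated to be 45, half of the sample will only be about 22 clinicians"; 22 is judged too few, so 25 is chosen. The trial may stop if the between-group comparison is significant at 5%, preferably 1%, with a reduction of at least 1.5 units in the intervention arm.

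The Sample size section shows where 45 comes from. First, "it is estimated that a sample size of 35 participants in each arm is required". Then: "Allowing for an attrition rate of 25%, and 5% for possible inclusion of covariates in the analyses", which brings the total to 90 clinicians, 45 per arm.

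Table 1 places T3, with its own chart audit, 12 weeks after the intervention ends. The Statistical methods section analyses the primary endpoint with a repeated-measures linear mixed model across time points.

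**The concern.** The numerator and denominator count different things. The 25 are clinicians who have already survived attrition to T2. The 45 are clinicians at enrolment, a number that was raised because a quarter are expected to be lost. Dividing one by the other makes the look appear earlier than it is.

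The section also defines its midpoint by completion of the trial, yet its trigger is T2, and a clinician at T2 still has T3 to come.

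This matters because the look can stop the trial. An efficacy boundary has to be tied to the fraction of information available, and this section gives a wrong account of the timing together with a level tied to no fraction. A stop on T2 data could also put at risk the randomised T3 comparison, which feeds both the primary model and the economic data collection.

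**Working it through.** **Inputs from the article.** Required per arm 35; attrition 25%; covariate allowance 5%; enrolled per arm 45; trigger 25 per arm with T2 data; difference 1.5, with 2.0 read as the SD; module up to 4 weeks; each audit 30 days; recruitment from 1 September 2018 to about 31 July 2019 (333 days).

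**Step 1. The plan's own figures.** 35 × 1.30 = 45.5, consistent with 45. Half of 45 is 22.5, the stated figure of about 22. The arithmetic reproduces; the choice of denominator is the problem.

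**Step 2. Like-for-like share of clinicians at T2.**
- Against the required number: 25/35 = 71.4%.
- Against expected completers: 45 × 0.75 = 33.75, and 25/33.75 = 74.1%.
- If no attrition occurs before T2: 25/45 = 55.6%.

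Half of 33.75 to 35 is 17 to 18 clinicians, not 22. A two-sided 5% test with 90% power, difference 1.5 and SD 2.0 needs 38 per arm by the normal approximation. Against 38 the share is 25/38 = 66%, still not half.

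**Step 3. From clinicians to information.** Suppose, for illustration, that each clinician carries equal weight, that the final contrast averages T2 and T3 with correlation ρ, and that the look has T2 only. The average has variance (1 + ρ)/2 times that of one time point, so the fraction is 25 × (1 + ρ)/2 divided by 33.75 or 35.

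| ρ | 25 × (1 + ρ)/2 | over 35 | over 33.75 |
|---|---|---|---|
| 0.3 | 16.25 | 46% | 48% |
| 0.5 | 18.75 | 54% | 56% |
| 0.7 | 21.25 | 61% | 63% |
| 1.0 | 25.00 | 71% | 74% |

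**Step 4. The stopping level.** Take two looks with test statistics correlated at the square root of the information fraction, a final test at 5%, and no effect-size condition. Overall two-sided type I error is then:
- interim at 5%: 8.3% at a fraction of 0.50, 8.1% at 0.556, 7.5% at 0.714, 7.4% at 0.741;
- interim at 1%: 5.5%, 5.4%, 5.2% and 5.2%.

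O'Brien-Fleming-type spending at 0.714 gives a two-sided interim level of 0.020 if 0.05 is spent as one function, and 0.016 if 0.025 is spent on each side. At 0.50 the values are 0.0056 and 0.0031.

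**Step 5. Enrolment at the look.** Assume uniform accrual, which the article does not state. The share enrolled is [25/(1 − d)/45 × 333 + lag]/333, where d is the attrition before T2 and the lag is in days.
- d = 0, lag 28 (module only): 213/333 = 64%.
- d = 0, lag 58 (module plus T2 audit): 243/333 = 73%.
- d = 0.125, lag 58: 269.4/333 = 81%.
- d = 0.25, lag 28: 274.7/333 = 82%.
- d = 0.25, lag 58: 304.7/333 = 91%.
- d = 0.25, lag 88 (T1 audit added): 334.7/333, so 100%.

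**The case against.** **The denominator can be partly defended.** The section does not call 25 exactly half: it puts half at about 22 and deliberately goes higher. The analysis is by intention to treat with multiple imputation, so all 45 per arm stay in the analysis set, and the outcome comes from chart audit. The article does not say when the 25% is lost. This stands in part, and it is why 56% is the lower end of the range. But imputation does not restore information lost to attrition, and the plan itself treats 35 as the number needed.

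**A reader might infer that the look falls at 71–74% of the information.** The documents do not support that. The primary model uses T3 as well as T2, on patient-level scores, and patients per clinician are not given. Step 3 shows that the fraction could be close to half, though that would be coincidence and not the reasoning the section offers.

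**A reader might infer that over 90% of clinicians would be enrolled by then, so that a benefit stop is pointless and should be deleted.** That is one scenario in a range of 64–100%. The article gives two dates, the later one approximate, and no accrual pattern. Nothing says that sites start one after another.

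**The stopping levels do not depend on any fraction, so the mislabelling does not by itself make them wrong.** This is correct. At a 71% fraction the preferred 1% is stricter than the spending values above. The 1.5-unit condition may also tighten the rule. If it means an observed between-arm difference, then with SD 2.0 and 25 per arm the standard error is 2.0 × √(2/25) = 0.566, and 1.5/0.566 = 2.65, a two-sided p of about 0.008. The section words it as a reduction in the intervention arm, however, so that reading is not secured, and 1% is only a preference.

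**The section does not say that a stop would end T3 follow-up.** Also correct: T3 is left unprotected, not cancelled.

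**Conclusion.** The point holds as an inconsistency in how the look is justified. A count of completers is set against an enrolment total that includes expected dropouts, and T2 is treated as completion of the trial. On the plan's own figures the look comes at 71–74% of evaluable clinicians per arm if all attrition precedes T2, and at 56% if none does. The information fraction is not fixed by the article; about 46–63% is illustrative and rests on averaging T2 and T3 with correlation 0.3–0.7.

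The practical weight comes from the stopping rule attached to the look. A flat 5% at the interim and again at the end gives about 7.5% overall at a fraction of 71%, and more at smaller fractions. That figure ignores the 1.5-unit condition; at the preferred 1% the excess is small. The change is worth making because it is cheap and protects both the error rate and the T3 comparison. The documents do not support removing the benefit stop on enrolment grounds.

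**What to change.** In the Interim analysis section:

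1. Drop the midpoint claim and the reference to having completed the trial. Describe the look as 25 of about 34–35 evaluable clinicians per arm at T2, and say what is assumed about attrition before T2.
2. Replace the flat 5%, preferably 1%, with an alpha-spending boundary computed at the actual information fraction of the planned primary analysis, and name the function and its sidedness. As an example, O'Brien-Fleming-type spending gives about 0.016–0.020 two-sided if that fraction is 71%, and less if it is lower. Alternatively, make the look non-stopping.
3. State that all enrolled clinicians continue to T3 under their randomised allocation whatever the interim result.

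The cost is a rewritten paragraph, a stricter interim threshold than 5%, and no early release of wait-listed clinicians.
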